#### Process measures

Process evaluation data will be collected from intervention schools using both quantitative and qualitative methods. The aim will be to document the implementation of the intervention, as well as to describe and compare processes occurring in the intervention and control schools, at school and participant level.

### Ethical considerations

Ethical approval will be obtained through the University of Leeds research ethics committee. Written informed consent from all schools as well as participants' parents will be sought prior to their enrolment into the study.

### Statistical Analysis

A random intercepts model of child-level outcomes will be used allowing for the hierarchical structure of the data caused by cluster randomisation: child within school. An extra level for the class is unnecessary because only one class is included from each school. MLwiN[15] will be used for this analysis. The fixed effect for the intervention group will be included in the model as a single covariate.

Balance of school and child-level variables between the two intervention groups will be assessed at baseline. This will be carried out with the following variables i) at school level: percentage of children with English as an additional language, percentage of non-white children, percentage of children with free school meals eligibility and percentage defined as having special educational needs ii) and at child level: sex, age and each of the primary and secondary child-level outcomes.

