**Method:**

This study is a cluster randomised controlled trial of Year 2 classes from 54 primary schools across England. The schools will be randomly allocated into two groups to receive either an active intervention called Project Tomato, to support maintenance of fruit intake in Year 3 children, or a less active intervention (control group), consisting of a 5 A DAY booklet. Children's diets will be analysed using the Child And Diet Evaluation Tool (CADET), and height and weight measurements collected, at baseline (Year 2) and 18 month follow-up (Year 4). The primary outcome will be the ability of the intervention (Project Tomato) to maintain consumption of fruit and vegetable portions compared to the control group.

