### Study procedure

Eligible schools will be sent a letter, additional information and a consent form inviting them to take part in the study. Consenting schools will then be contacted to arrange an appropriate day to collect baseline information from the children. A study recruitment form will also be sent to the schools/Year 2 teachers. The teacher will use this form to record which children obtained parental consent and which children were absent on the CADET day. Parental, opt-out consent will be obtained prior to data collection. Baseline dietary information using CADET and anthropometric measures of the children will be collected by the fieldworker in the school.

Following baseline data collection, the randomly selected schools for the trial will be sent a letter informing them whether they are in the active or less intensive intervention. The allocation sequence will be generated by the trial statistician. All schools will be allocated at the same time. Time between notification of allocation and receiving the first intervention material will be kept to a minimum to minimise withdrawals at that stage.

Blinding of the schools to their intervention group will not be possible because of the nature of the intervention. Fieldworkers will be blinded to the allocation of schools to the intervention and control arms of the study. Schools will be followed up 18 months later when the sample of children are in year 4 (aged 8–9 years). They will have further measures of diet using CADET and anthropometric measures taken.

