### Outcome measurements

#### Primary outcome

The primary outcome will be the ability of the intervention (Project Tomato) to maintain consumption of fruit and vegetable portions following the exit of children from the SFVS over 18 months compared to the control group.

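### The effect model has the intervention group as its only fixed effect, so baseline intake, weight and BMI are checked for balance but not adjusted for, at a cost in precision

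*Protocol article*

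**What the plan says.** All references are to the protocol article.

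- **Model (Statistical Analysis).** The section first sets out the structure: "A random intercepts model of child-level outcomes will be used allowing for the hierarchical structure of the data caused by cluster randomisation: child within school". The fixed part follows: "The fixed effect for the intervention group will be included in the model as a single covariate". No baseline value, stratification factor or other covariate is named for this model.
- **Baseline data (Study procedure).** "Baseline dietary information using CADET and anthropometric measures of the children will be collected by the fieldworker in the school". Schools learn their allocation only after this. The Abstract gives the same measurements at Year 2 and, 18 months later, at Year 4.
- **Use of baseline values (Statistical Analysis).** "Balance of school and child-level variables between the two intervention groups will be assessed at baseline", covering at child level "sex, age and each of the primary and secondary child-level outcomes". No consequence of an imbalance is stated.
- **Primary outcome.** The ability of the intervention to "maintain consumption of fruit and vegetable portions following the exit of children from the SFVS over 18 months compared to the control group".
- **Exception (Children's attitudes).** The attitude items are analysed at two time points, so baseline does enter that analysis.

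**The concern.** The question is whether intake holds up after Year 2, so a child's Year 2 intake is the natural prognostic covariate. It is measured before allocation is known, so adjusting for it is safe. A model with the group term alone ignores it. The standard error is then wider than it need be, and any chance difference between arms at baseline passes, in part, into the estimated effect.

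A balance check with no stated consequence does not deal with this. If an imbalance appears, the choice between adjusting and not adjusting is made after the data have been seen.

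The article does not leave the covariate set open for an analysis plan to fill. It states one.

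**Working it through.** **Inputs from the Sample size section:** 25 children per school; design effect 3.4; 500 children per group for 90% power at 0.5 portion; 75% retention; 27 schools per group.

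**Not stated, so assumed:** two-sided alpha of 0.05; baseline SD and intraclass correlation (ICC) equal to those at follow-up; baseline-to-follow-up correlations over a range.

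**1. The plan's own figures.**
- ICC = (3.4 − 1)/(25 − 1) = 0.10.
- Effective children per group = 500/3.4 = 147.
- Implied SD = 0.5 × √(147/2)/(1.960 + 1.282) = 1.32 portions.
- Schools: 500/25 = 20; 500/0.75 = 667 children, and 667/25 = 26.7, rounded to 27.

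The SD is back-solved, so the 500 is not independently tested. The other steps reproduce, and the 500 is consistent with an unadjusted comparison of two means.

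**2. Variance with baseline adjustment.** Set the total variance to 1. With 25 × 0.75 = 18.75 analysed children per school, the variance of a school mean is 0.10 + 0.90/18.75 = 0.10 + 0.048 = 0.148. With school-level correlation rs and child-level correlation rw, the adjusted variance is 0.10(1 − rs²) + 0.048(1 − rw²).

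| rs / rw (assumed) | Adjusted variance | Ratio to 0.148 | Reduction |
|---|---|---|---|
| 0.3 / 0.2 | 0.0910 + 0.0461 = 0.1371 | 0.926 | 7% |
| 0.5 / 0.3 | 0.0750 + 0.0437 = 0.1187 | 0.802 | 20% |
| 0.7 / 0.4 | 0.0510 + 0.0403 = 0.0913 | 0.617 | 38% |

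This formula lets each level have its own slope and treats the school effect as known, so it is slightly favourable. Two checks use the covariance of baseline and follow-up school means, c = 0.10rs + 0.048rw, which is 0.0396, 0.0644 and 0.0892 in the three rows:
- Adjusting for the observed school-mean baseline gives a ratio of 1 − (c/0.148)² = 0.928, 0.811 and 0.637, a reduction of 7%, 19% and 36%.
- Adjusting for the child's baseline alone, with slope about rw, gives (0.148 − 2·rw·c + 0.148·rw²)/0.148 = 0.933, 0.829 and 0.678, a reduction of 7%, 17% and 32%.

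**3. Effect on power.** Take 500 per group, SD 1.32 and the same correlation r at both levels, so that the variance factor is 1 − r². Power rises from 90.0% to 91.1% (r = 0.2), 92.5% (r = 0.3) and 96.3% (r = 0.5).

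**4. Chance baseline imbalance.**
- Using the 500 per group: SE = 1.32 × √(2 × 3.4/500) = 0.154 portion.
- Using 27 schools of 25 per group: √(2 × 1.75 × (0.10/27 + 0.90/675)) = 0.133 portion, where 1.75 is the squared SD.

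Only the share predicted by baseline, r × imbalance, reaches the unadjusted estimate. For a one-SE imbalance of 0.154 this is 0.05 portion at r = 0.3 and 0.08 at r = 0.5. With 0.133 it is 0.04 and 0.07.

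**The case against.** **Validity is not at issue.** Randomisation makes the unadjusted estimate unbiased, and the sample size does not rely on adjustment. This stands. At the low end of the assumed correlations the gain is small.

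**The sentence may describe coding.** It sits beside remarks on hierarchy and might mean only that the group enters as one fixed term without a random slope. That is possible, and an adjusted model may exist in an analysis plan that is not shown. But no other covariate is named for this model, and the plain reading is a group-only model. If coding was meant, the sentence still needs correcting.

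**The outcome may be a change score.** Since the aim is maintenance, the modelled quantity could be change, and baseline would then enter implicitly. The article does not say so. A reader might go on to infer that a change score must be worse than an unadjusted comparison whenever the overall correlation is below 0.5. That rule does not carry over to clustered data. At 0.7/0.4 the overall correlation is 0.10 × 0.7 + 0.90 × 0.4 = 0.43, yet the change-score variance is 2 × 0.10 × 0.3 + 2 × 0.048 × 0.6 = 0.118, below 0.148. At 0.3/0.2 it is 2 × 0.10 × 0.7 + 2 × 0.048 × 0.8 = 0.217, well above. Baseline adjustment has the smaller variance in both cases.

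**Stratification already helps.** Randomisation is stratified on ethnicity and deprivation, so the imbalance will be smaller than shown to the extent that these predict intake. This stands, and the stratification factors are themselves absent from the stated model.

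**Conclusion.** The point holds as a matter of efficiency. The article fixes a group-only model and leaves pre-allocation baseline intake, weight and BMI out of it. Adjustment would cut the variance of the intake effect by about 7% to 38%; the upper end is nearer 32% if only the child's own baseline is used. It would also remove a carry-over of roughly 0.05 to 0.08 portion per one-SE baseline imbalance. These sizes rest on the ICC of 0.10 implied by the article, on a back-solved SD of about 1.32, and on correlations that the article does not give.

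Four stronger readings are tempting and are not supported:
- **A biased or underpowered trial.** Neither is shown.
- **An error of about ±0.26 portion in the effect** (1.96 × 0.133). That is the 95% range of the baseline difference; only a fraction of it carries over.
- **A several-fold loss for weight and BMI.** Strong tracking within children affects only child-level variance. For intake, 0.10/0.148 = 68% of the variance of a school mean lies between schools. The article gives neither an ICC nor a correlation for weight or BMI, so no multiple can be stated.
- **Baseline data held on every child and unused for every secondary outcome.** Consent is opt-out and absences are recorded, and the attitude analysis does use both time points.

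**What to change.** Replace the sentence on the fixed effect with wording such as: *The primary analysis is a random-intercepts model (child within school) of follow-up daily fruit and vegetable portions, with fixed effects for intervention group, the child's baseline portions and the two randomisation stratification factors.* The stratification factors are preferable rather than essential. The school-mean baseline is an optional further term that recovers the remaining gain if school-level tracking is stronger than child-level tracking.

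Use the same form, with the matching baseline value, for nutrients, weight and BMI. Keep the group-only model as a sensitivity analysis, and say that the balance table is descriptive and does not decide the covariates.

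The cost is one or two sentences, fixed before the follow-up data are seen. The data are already to be collected, and no extra schools or children are needed.

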### Sample size

From the nationally representative sample, a sub-set of schools will be recruited into the intervention trial. Cluster randomisation will be used, randomising at the school level, as the intervention will involve whole lesson plans and school-level policies. A sample of 25 children (one Year 2 class) from each school, will give a design effect of approximately 3.4 to take account of the cluster randomisation. To have 90% power to detect a 0.5 portion difference in fruit intake, 500 children per group are required, i.e. about 20 schools in each group. Based on results from our initial evaluation of the SFVS, 75% who completed CADET at baseline also completed the follow up CADET. To allow for this margin of safety, 27 schools per group will be selected in each group, i.e. 54 schools in total. The size of effect the study is powered to detect (one half of a portion of fruit/vegetable) was chosen because it was considered the smallest improvement in intake that was worthwhile detecting with an achievable sized sample, and considering the nature of the intervention.

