### Randomisation

To ensure balance on important potential confounders within the trial, block randomisation within strata will be used, stratifying on measures of ethnicity (% non-white) and deprivation (% Free School Meals), both split at the median. Whilst we would like to stratify on variables such as region and achievement, there are not enough schools to give large enough strata to do this. Block randomisation will use block sizes of two because allocation will take place in one go, so there will be no opportunity for prediction of which group the schools will be in.

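### The stated model omits the ethnicity and deprivation strata used to randomise schools; if the strata predict intake, its standard error is too large and its test conservative.

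*Protocol article*

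**What the plan says.** Under Randomisation, the protocol article states the purpose of stratifying, "To ensure balance on important potential confounders within the trial", and the factors: "stratifying on measures of ethnicity (% non-white) and deprivation (% Free School Meals), both split at the median". Two median splits give four strata. It adds: "Block randomisation will use block sizes of two because allocation will take place in one go". The arms will therefore be almost exactly balanced within each stratum.

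Under Statistical Analysis, the model is described thus: "A random intercepts model of child-level outcomes will be used allowing for the hierarchical structure of the data caused by cluster randomisation: child within school". On its fixed part the section says: "The fixed effect for the intervention group will be included in the model as a single covariate".

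The percentages of non-white pupils and of pupils eligible for free school meals appear again in that section, but only in a list of variables to be compared between arms at baseline. No section places them in the model.

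**The concern.** Stratified allocation in small blocks forces the strata to be nearly equal between arms, so differences between strata contribute almost nothing to the true variance of the arm comparison. A model without the strata cannot see this. It estimates the school-level variance from all the differences among schools, including those between strata, and builds the standard error from that total. The estimate is sound, but its stated uncertainty does not match the design.

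At stake are confidence intervals wider than they need be and p-values larger than they should be. This matters most for a null or borderline result, which the Discussion says would be used to shape the research agenda and future strategies.

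**Working it through.** **Inputs from the protocol article, Sample size and Randomisation.** 25 children per school; a class of that size "will give a design effect of approximately 3.4 to take account of the cluster randomisation"; 500 children per group for 90% power to detect 0.5 portion; 75% completing follow-up; 27 schools per group, 54 in total; blocks of two in four strata.

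**The plan's own figure.** 500 / 25 = 20 schools per group; 20 / 0.75 = 26.7, rounded up to 27. This reproduces.

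**Derived quantities.**
- Intracluster correlation implied by the design effect: (3.4 − 1) / (25 − 1) = 0.10.
- Children analysed per school: 25 × 0.75 = 18.75, about 19.
- Standard deviation implied by the sample size, assuming a two-sided 5% test (neither the standard deviation nor the significance level is stated): effective number per group 500 / 3.4 = 147; 0.5 / [(1.960 + 1.282) × √(2/147)] = 1.32 portions.
- Between-school share of the variance of a school mean: 0.10 / (0.10 + 0.90/18.75) = 0.10 / 0.148 = 0.676.

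**Assumed quantity.** R² is the share of between-school variance that the strata explain. The protocol gives no value, so it is varied from 0 to 0.5.

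**Large-sample approximation.** Allocation removes a fraction f = R² × 0.676 of the variance of the arm difference. The unadjusted standard error is then too large by the factor 1/√(1 − f), and the true level of the 5% test is 2 × [1 − Φ(1.96/√(1 − f))].
- R² = 0.2: f = 0.135, factor 1.075, level 3.5%.
- R² = 0.4: f = 0.270, factor 1.171, level 2.2%.

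**Simulation.** 54 schools, strata of 14, 13, 13 and 14 (assumed), blocks of two, 19 children per school, intracluster correlation 0.10. School means were analysed, which is equivalent to the random-intercepts model when clusters are of equal size. There were 30,000 runs per scenario under no effect and 6,000 per scenario for power at 0.5 portion (not run at R² = 0.2). The tests are t tests.

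| R² | Model SE / true SE, no strata | Type I error, no strata | Power, no strata | Power, with strata |
|---|---|---|---|---|
| 0 | 0.99 | 5.1% | 93.5% | 93.5% |
| 0.1 | 1.03 | 4.3% | 94.6% | 95.4% |
| 0.2 | 1.08 | 3.6% | – | – |
| 0.3 | 1.14 | 2.6% | 96.6% | 98.0% |
| 0.5 | 1.25 | 1.4% | 97.2% | 99.3% |

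With the four strata as fixed effects, the model SE / true SE is 0.99 to 1.01 and the type I error 4.8 to 5.1% at every R² tried.

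The mechanism shows in the standard errors, in units of the outcome's standard deviation. From R² = 0 to R² = 0.5, the true standard error of the unadjusted estimate falls from 0.105 to 0.084, but the one the unadjusted model reports stays at 0.104 to 0.106.

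**Choice of test.** With a Wald z test on maximum-likelihood estimates, the unadjusted level is 6.2, 5.1, 4.4, 3.2 and 1.8% for R² = 0, 0.1, 0.2, 0.3 and 0.5. With the strata added it is 7.0, 6.8, 6.9, 6.6 and 6.5%. The small-sample inflation of the z test partly hides the conservatism of the unadjusted model.

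**The case against.** **The sentence may describe coding only.** It could mean that group enters as one indicator, leaving other covariates to a fuller document that is not shown. The wording allows this, and it does not say that the analysis is unadjusted. But the section sets out the hierarchy, the software and the fixed effect, names no other covariate, and mentions the stratification variables only for a balance check. As printed, the model does not match the allocation; if coding was all that was meant, the sentence needs clarifying.

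**The effect is conditional.** A reader might infer that the standard errors are certainly too large and the level certainly below 5%. The documents do not support that. At R² = 0 there is no effect, and with a Wald z test the level is still about 5% at R² = 0.1. The protocol names neither the test nor the strength of the strata. What it does do is call the strata important potential confounders, which implies that they are expected to predict intake.

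**The consequence is modest.** This stands. The omission causes no bias and no excess of false positives, and the power lost is 0.8 points at R² = 0.1, 1.4 at 0.3 and 2.1 at 0.5.

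**Two further inferences fail.** A reader might conclude that the benefit of stratifying is thrown away. It is not: the unadjusted estimate still gains precision from the allocation, and only the reported standard error fails to credit it. Nor is most of the variance at school level. The implied share of outcome variance is 10%; the 68% above is a share of the variance of a school mean.

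**Conclusion.** The point holds in conditional form. The allocation uses the strata and the stated model does not, so to the extent that the strata predict intake the reported standard error is too large and the test conservative. For R² of 0.1 to 0.5 and a t test, the excess in the standard error is about 3 to 25% and the type I error about 4.3 to 1.4%. At R² = 0 there is nothing to correct.

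These sizes rest on an assumed R², an intracluster correlation back-calculated from an approximate design effect, equal numbers of children per school and assumed stratum sizes. The power figures also rest on an assumed two-sided 5% level. Since the error is conservative and power stays above 90% throughout, this is an inexpensive improvement and no threat to the trial's validity.

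**What to change.** In Statistical Analysis, state that the random-intercepts model includes, besides intervention group, the two stratification factors as fixed effects, coded as the median-split indicators used in the allocation. Apply this to the primary outcome and to the other child-level outcomes analysed with that model. Children's attitudes are to be analysed by multivariate analysis of variance, so this clause would not reach them.

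The return to a 5% level was shown with a t test on school-level degrees of freedom; a Wald z test on maximum-likelihood estimates gave 6.5 to 7.0% with the strata included. The same clause could therefore name the reference distribution.

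The cost is one clause. The variables are already held for every randomised school because the allocation needs them. The unadjusted model has 54 − 2 = 52 school-level degrees of freedom; two indicators use 2 of them, and four separate strata use 3. Fixing the covariates before outcome data are seen also removes any discretion over adjustment after the baseline balance check.

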#### Process Measures

Stata version 10.1 and MLwiN will be used to analyse process evaluation variables compared with the fruit and vegetable results from CADET. Process measures and feedback on the intervention will be analysed using appropriate statistical methods[16,17].

#### Children's attitudes

The ten items relating to children's attitudes to fruit and vegetables will be analysed using factor analysis to identify the underlying structure of their responses. Kaiser-Meyer-Olkin and Bartlett's test of sphericity will be used to assess the suitability of the data for factor analysis. Kaiser's criterion and scree plots will be used to determine the number of factors extracted. For each factor, internal consistency will be measured using Cronbach's alpha, as there will be a number of potential outcomes assessed with possibly more than one identified factor, this will be repeated at two time points. Then a multivariate analysis of variance will be performed to determine whether the intervention has a differential effect on children's attitudes over time.

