#### Behavioural

Children's attitude to fruit and vegetable consumption as measured by a set of ten questions embedded in CADET[14].

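### The attitude outcome is to be tested by a multivariate analysis of variance with no allowance for school, at odds with the random-intercepts rule for child-level outcomes

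*Protocol article*

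**What the plan says.** Three statements in the protocol article bear on this point.

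- **Unit of randomisation.** Under Sample size: "Cluster randomisation will be used, randomising at the school level". The same section says that 25 children per school "will give a design effect of approximately 3.4 to take account of the cluster randomisation".
- **General analysis rule.** The Statistical Analysis section states the rule: "A random intercepts model of child-level outcomes will be used allowing for the hierarchical structure of the data caused by cluster randomisation: child within school". MLwiN is the named software.
- **Attitude analysis.** Attitudes are a secondary outcome measured on each child. The Behavioural section describes them as "Children's attitude to fruit and vegetable consumption as measured by a set of ten questions embedded in CADET". Under Children's attitudes, the ten items go through factor analysis, and the intervention is then tested: "Then a multivariate analysis of variance will be performed to determine whether the intervention has a differential effect". That section mentions no school level, random effect, cluster adjustment or multilevel software, and does not say how its test relates to the random-intercepts model.

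The article gives no ICC for attitudes or for their change over time, and no significance level or sidedness.

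**The concern.** A multivariate analysis of variance deals with correlation among factors, and between occasions, within one child. It does not deal with correlation among children in the same school. With 54 schools and 25 × 0.75 = 18.75 children per school at follow-up, about 54 × 18.75 ≈ 1,010 children would count as independent observations in a comparison where only 54 units were randomised.

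This is more than detail left to a fuller document. The article names a method for this outcome, and that method in its usual form is not the one the article requires for outcomes of this kind. An analyst who follows the attitudes section literally would run a test that rejects a true null hypothesis too often. At stake is a false claim that the intervention changed attitudes, the only outcome listed under the Behavioural heading.

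**Working it through.** **1. The plan's own clustering figures.** Inputs from Sample size: design effect 3.4, 25 children per school, 500 children per group, 75% follow-up.

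- Implied ICC = (3.4 − 1)/(25 − 1) = 0.10.
- Schools per group = 500/25 = 20. Allowing for loss, 20/0.75 = 26.7, rounded up to 27, so 54 in total. Both counts reproduce.
- The 500 per group cannot be checked independently, because no SD is stated. Working backwards with an assumed two-sided 5% level and 90% power, 500/3.4 = 147.1 effective children per group. This gives SD = 0.5/[(1.960 + 1.282) × √(2/147.1)] ≈ 1.32 portions.

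So the sample size can be read as allowing for clustering. The figure of 3.4 is stated for fruit intake, not for attitudes.

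**2. Type I error of an unadjusted test.** Assumptions: nominal two-sided 5%; m = 19 analysed children per school (18.75 rounded); p attitude factors sharing a common ICC. With two occasions, the group-by-time test is a test on change scores, so the relevant ICC is that of the change.

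- Design effect: DE = 1 + (m − 1) × ICC.
- True error = P(χ²_p > c_p/DE), where c_p is the 5% critical value (3.841, 5.991 and 7.815 for p = 1, 2, 3).
- Example, ICC 0.10: DE = 1 + 18 × 0.10 = 2.80. For p = 1, 2 × [1 − Φ(1.96/√2.80)] = 24.1%. For p = 2, exp(−5.991/(2 × 2.80)) = 34.3%.

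| Assumed ICC | DE | 1 factor | 2 factors | 3 factors |
|---|---|---|---|---|
| 0.005 | 1.09 | 6.0% | 6.4% | 6.7% |
| 0.01 | 1.18 | 7.1% | 7.9% | 8.5% |
| 0.02 | 1.36 | 9.3% | 11.0% | 12.5% |
| 0.05 | 1.90 | 15.5% | 20.7% | 25.0% |
| 0.10 | 2.80 | 24.1% | 34.3% | 42.5% |

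**3. Check by simulation.** 27 schools per arm, 19 children per school, assumed between-factor correlation 0.3, 3,000 runs, Hotelling's T² (the two-group multivariate analysis of variance). The unadjusted test is compared with the same test on school means.

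| ICC | Unadjusted, 1/2/3 factors | School means, 1/2/3 factors |
|---|---|---|
| 0 | 5.0/5.7/4.6% | 5.1/5.6/4.6% |
| 0.01 | 6.8/7.1/8.9% | 4.4/4.2/5.0% |
| 0.02 | 9.0/11.9/13.4% | 4.9/5.1/6.0% |
| 0.05 | 15.1/19.4/24.1% | 5.0/4.3/5.2% |
| 0.10 | 23.6/34.9/42.1% | 5.1/5.3/4.4% |

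A further simulation of 4,000 runs at ICC 0.05 gave 14.9/21.0/25.6% unadjusted. The Monte Carlo standard error near 5% is √(0.05 × 0.95/3000) ≈ 0.4 percentage points, so formula and simulation agree. The school-means test stays at about 4-6% throughout, so the excess comes from the missing school level and not from testing several factors jointly.

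**The case against.** **The general rule may govern.** The Statistical Analysis section speaks of child-level outcomes without exception, and attitudes are one of them. Multilevel and school-level forms of a multivariate comparison exist, and a condensed article may leave the choice to a fuller document. A reader might infer that the authors decided to ignore clustering. The article does not say so; it is silent. What remains is that a specific instruction, under its own heading, names a different analysis from the general rule. On either reading the two sections need reconciling.

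**The size is unknown.** A reader might infer an error rate far above 5%, or apply the design effect of 3.4 and obtain 2 × [1 − Φ(1.96/√3.4)] = 28.8% for one factor. The article does not support that for attitudes. The 3.4 belongs to fruit intake at 25 children per school. Even the same ICC of 0.10 gives about 24% at 19 children, and an ICC of 0.005 to 0.01 gives only about 6-9%. This objection stands: the direction is certain for any positive ICC, but the amount is conditional.

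**Factor structure.** The words "this will be repeated at two time points" might be taken to mean that factors are extracted separately at baseline and follow-up, so that change scores would not share a scale. In context the phrase most naturally refers to the Cronbach's alpha check just before it, and separate extraction is not stated. No finding is made on this.

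**Consequences.** A reader might fear that a spurious attitude effect would be reported as the mechanism of the intervention. The article plans no mediation analysis and does not give attitudes that role.

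**Conclusion.** The point holds as a conflict between two sections. The attitude test is named in a form that, taken literally, leaves out the school level, while the plan's own rule for child-level outcomes is a model "allowing for the hierarchical structure of the data caused by cluster randomisation: child within school". Such a test is anti-conservative for any positive school ICC. Its true error at a nominal 5% runs from about 6-7% (ICC 0.005) to 24-43% (ICC 0.10) for one to three factors. These figures assume about 19 analysed children per school, a two-sided 5% level and a common ICC across factors. The article gives no value that would place attitudes within this range. One secondary outcome is affected; the primary outcome, the sample size and the model stated for the other child-level outcomes are not.

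**What to change.** Amend the Children's attitudes section so that its intervention test follows the Statistical Analysis section. Any of these would do:

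- a random-intercepts model, child within school, for each attitude factor score;
- a multivariate multilevel model in MLwiN, if one joint test across factors is wanted;
- a multivariate analysis of variance on school-level means, as a simpler joint test.

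For the first option, adjustment for the baseline score is preferable, since that score is already collected. This is a recommendation beyond the stated model, which mentions only the intervention effect as a covariate. If a multivariate analysis of variance that allows for school was intended all along, one sentence saying how school enters is enough.

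The cost is a change of wording. The software is already planned, and no further schools, children or data are needed. The downside is larger, but valid, p-values for this secondary outcome.
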